# PROTOCOL SYNOPSIS

| **TITLE** | SNOTWATCH: Mapping real-time respiratory microbiology information to inform health outcomes |
| --- | --- |
| **STUDY DESCRIPTION** | We aim to use retrospective, unlinked datasets which report on health outcomes and respiratory PCR results. These two datasets are linked based on date of presentation as well as location to create one large dataset.  This enables easy data visualisation and statistical analysis.  Statistical analysis involves fit testing of our data and application of techniques which determine how well viruses can predict the health outcomes of interest. Statistical analysis may be conducted on temporal data only or on spatiotemporal data. |
| **OBJECTIVES** | To examine and describe organism specific epidemiology of respiratory and gastrointestinal positive tests from all participating laboratories.  To describe the association of organisms in time and place with health service utilisation and presentations. |
| **OUTCOMES AND OUTCOME MEASURES** | - Outcomes are the statistical association between respiratory virus and a health outcome of interest. This will be stratified based on temporal-only association and spatiotemporal associations. - Outcomes also include qualitative associations found between viruses and health outcomes, represented visually. - Associations between health outcomes and month of the year may also be calculated as appropriate. - Health outcomes may also be analysed in relation to other predictive variables depending on the specific illness being studied. |
| **STUDY POPULATION** | De-identified pathology and clinical presentations data received from the entire State of Victoria |
| **DESCRIPTION OF SITES ENROLLING PARTICIPANTS** | Multiple levels of health care including state-wide infectious disease surveillance services, telephone health advice operators, private and public pathology services, general practitioners (GP), ambulance services, emergency department and hospital admission data. |
| **STUDY DURATION** | SNOTWATCH is an ongoing platform for analysing various health outcomes in the community with virus circulation. |
| **PARTICIPANT DURATION** | As per each institutional research agreement. |

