# INTRODUCTION AND BACKGROUND

# Background and rationale

Recent years have seen a widespread uptake of respiratory (and gastro-intestinal) pathogen molecular diagnostic tests that test for multiple potential pathogens for each sample. Not only does this increase the breadth or organisms tested for, but the increased sensitivity of this testing for DNA or RNA of these organisms has vastly increased the number of positive tests.

This has allowed the availability of surrogate population level data regarding the distribution of many common pathogens across time and place, with most hospitals and community pathogen providers in Victoria utilising these assays. It is now feasible technically to de-identify these data and amalgamate all results to improve our understanding of how these organisms circulate each year.

At the same time, our ability to examine location specific health events from multiple levels of health care provision has improved. These include calls to telephone health advice lines, general practitioner (GP) presentations, ambulance encounters, emergency department presentations and hospital admission data.

This now means we have the opportunity to examine associations between potential pathogens and patterns of health care presentations using geo-temporal statistical methodologies with completely deidentified, non-linked data. This has the advantage of observing all patients’ privacy while still having the potential to upload, aggregate and examine real-time data.

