### 4.5.7. Inclusion Criteria

Any respiratory or gastrointestinal multiplex PCR assay microbiological test performed by participating pathology services may be included. All VAED and VEMD records, and all ED encounters from participating datasets will be included. POLAR GP participating practices have an opt-in mechanism for declaring they are willing for their de-identified data (which does not identify the practice or GP) to be utilized for POLAR GP research council approved research projects. Individual patients at each practice have the ability to opt-out, in which case their data is not uploaded to the POLAR-GP data warehouse and will not be available for research.

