### 4.5.8. Exclusion Criteria

Patients who opt out of POLAR GP are the only exclusion criteria.

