# 7.2. Benefits to participants

This study does not present any direct benefit to the participants however the study does provide an opportunity to gain a better understanding of:

- The typical seasonal pattern of spread of specific infections, allowing better information to be provided to community and health care providers (HCP), possibly enabling early warnings to increase preventive care such as asthma medications or vaccinations
- Awareness of what is circulating locally at the current time, potentially improving decisions regarding prescribing (or not prescribing) antibiotics and antivirals
- The specific impact of organisms upon health conditions and health service utilization, allowing better planning, provisioning and targeted timely communications to patients, families, and HCP

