# 11. DATA ANALYSIS

## 11.1. Sample size and statistical power

In line with the SNOTWATCH aims the focus will be on attaining retrospective data within a timeframe of 7-10 years dating from the enrolment of each participating site/dataset. SNOTWATCH prospective phase is an ongoing epidemiological/ecological analysis which will map viral respiratory and GI microbiology results in real-time to inform health outcomes registered in Victorian health datasets. For instance, most of the results will come from individuals who have hospital records located in either VAED or VEMD datasets that can be linked to analyse respiratory outcomes. A smaller subset of individuals will have primary care records located in POLAR, and BloodSTAR (National Blood Authority) that can be linked to further analyse rare paediatric health outcomes.

The investigators aim to collaborate with other Australian jurisdictions in the future to increase the sample size. SNOTWATCH will involve a much larger population than any other viral respiratory disease surveillance method in Australia. The large sample size will have significant statistical advantages including increased precision of estimates and lower random error.

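### A positive test taken at a counted hospital or ED presentation can enter both the exposure and the outcome series, and the upload fields give no reliable way to separate such tests

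*Protocol*

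**What the plan says.** - **Join.** The Protocol synopsis (Study description) says: "These two datasets are linked based on date of presentation as well as location to create one large dataset". It states the purpose as "application of techniques which determine how well viruses can predict the health outcomes of interest".
- **Source of tests.** Section 11.1 says, as an illustration, that "most of the results will come from individuals who have hospital records located in either VAED or VEMD datasets". VAED and VEMD are also outcome datasets (4.3.3).
- **Inclusion and exclusion.** Section 4.5.7: "All VAED and VEMD records, and all ED encounters from participating datasets will be included". Section 4.5.8: "Patients who opt out of POLAR GP are the only exclusion criteria". Neither removes a test ordered at a counted encounter.
- **Test-side fields.** Sections 4.3.2 and 4.4.2 list age, postcode, gender, date of test and positive results. Neither lists who requested the test or an encounter key.
- **No person-level match.** Section 2.1 describes "geo-temporal statistical methodologies with completely deidentified, non-linked data".
- **Objectives.** The primary objective (3.1.1) is descriptive. The secondary objectives (3.1.2) include the geo-temporal association of organism activity with health outcomes and service use, including admissions and ED presentations.
- **Methods.** Section 11.2 leaves full statistical methods to a separate SAP, which is not available here.

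**The concern.** Take a patient who attends an ED with asthma or an acute myocardial episode and is swabbed there. The visit adds one to the outcome count for that area and date. If the swab is positive, even by coincidence, it also adds one to organism activity for the same area and date. Counts built this way correlate even when circulation has no effect on presentations. This is separate from how much testing is done: with complete test denominators the same patient would still be on both sides.

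The secondary association objective for hospital and ED outcomes is at stake, and with it the synopsis wording that the analysis will "determine how well viruses can predict the health outcomes of interest". Part of such an association could be the outcome counted a second time. Overlap should be smaller for telephone-advice and GP outcomes, and the primary objective does not depend on the join.

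A SAP can choose models and lags, but it cannot split tests by a field that was never uploaded. The field lists are set in this protocol.

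**Working it through.** The protocol gives no figure for the overlap, so there is nothing to reproduce. The check asks how large an association could arise with no organism effect.

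**Model.** In one area and period:
- O = counted presentations for the outcome analysed, Poisson with mean λ and unrelated to circulation.
- Each presentation is tested and positive with probability pq, so positives from the outcome itself are Binomial(O, pq).
- All other positives are independent of O, and are set so that a share h of all positives comes from O. T is total positives.

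**Inputs.** pq and h are assumptions. Section 11.1 says only that a majority of results come from people with hospital records. h must be the share of positives from the specific outcome analysed, not from all hospital tests.

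**Same-date correlation.**
- Cov(O, T) = pq × λ
- Var(O) = λ and Var(T) = pq × λ / h
- Corr(O, T) = pq × λ / sqrt(λ × pq × λ / h) = sqrt(pq × h)

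| pq | h | sqrt(pq × h) |
|---|---|---|
| 0.10 | 0.05 | sqrt(0.005) = 0.07 |
| 0.05 | 0.5 | sqrt(0.025) = 0.16 |
| 0.10 | 0.6 | sqrt(0.06) = 0.24 |

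The first row suits one diagnosis that supplies few of the positives. The other two need an outcome broad enough to supply half or more of them. Simulation over 400,000 periods agrees with the formula (for example 0.158 against 0.160 at pq = 0.05, h = 0.51).

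**Would it be noticed?** With 365 daily points and a two-sided 0.05 test, the chance of a significant result is Φ(atanh(r) × sqrt(362) − 1.96):
- r = 0.071: Φ(1.35 − 1.96) = 0.27
- r = 0.158: Φ(3.03 − 1.96) = 0.86

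**Does a lag remove it?** With serially independent counts the lag-1 correlation is zero. Respiratory presentations are seasonal, so let the rate be lognormal around λ with log-SD σ and lag-1 autocorrelation 0.9 on the log scale. Write v = λ²(exp(σ²) − 1) and c = λ²(exp(0.9σ²) − 1). Then

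lag-1 correlation = pq × c / sqrt[(λ + v)(pq × λ / h + pq² × v)].

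With λ = 50, pq = 0.10, h = 0.6:
- σ = 0.1: v = 25.1, c = 22.6. Result 2.26 / sqrt(75.1 × 8.58) = 0.09.
- σ = 0.3: v = 235.4, c = 210.9. Result 21.1 / sqrt(285.4 × 10.69) = 0.38.

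With h = 0.05 and σ = 0.3 the result is 21.1 / sqrt(285.4 × 102.35) = 0.12. Simulation gives 0.09, 0.38 and 0.12. There is still no organism effect. Positives independent of the counted encounters correlate with O at about 0 in the same runs, as the model implies.

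**The case against.** **The join is a dataset key, not an analysis rule.** This stands. A table keyed by date and place can be lagged, and lag structure is SAP content. A reader might infer that the protocol commits to same-date analysis and so can never show precedence. The documents do not support that. The missing request setting is different, because the SAP cannot supply it.

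**Early warning does not rest on this join.** This stands. Section 7.2 speaks of "possibly enabling early warnings to increase preventive care" in its bullet on typical seasonal patterns, which draws on descriptive epidemiology. It is tempting to read this as a forecasting claim that the join defeats, but the text does not tie the two together. The formal objectives speak of description and association; only the synopsis wording speaks of prediction, and that can mean statistical prediction.

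**Having a hospital record is not being tested at the counted visit.** This stands. A reader might infer from 11.1 that most tests are duplicated in the outcome. The sentence does not say so. Overlap can occur; how much is unknown.

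**Partial proxies exist.** Data arrive by pathology organisation, 9.2.1 mentions diagnosis among information to be included with test results, and Appendix 16.1 requests investigations performed from the three site ED systems. These weaken any claim that separation is impossible. They do not make it reliable: one laboratory may serve both hospital and community, and the site ED fields cover neither VAED nor VEMD.

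**Conclusion.** The concern holds in a limited form. For hospital and ED outcomes under the secondary objective, the protocol lets a positive test from a counted presentation enter both series, and its upload fields do not allow such tests to be reliably identified. The uploading laboratory is at best a crude proxy.

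The size cannot be determined from the documents. Under the null model with assumed inputs, the spurious same-date correlation runs from about 0.07 for an outcome supplying 5% of positives to 0.24 for one supplying 60%, both at pq = 0.10. Extra-Poisson variation in presentations would raise these values. For narrowly defined diagnoses the effect may be small. Lagging alone is not a sound remedy: with autocorrelated presentations the overlap still produced lag-1 correlations of 0.09 to 0.38 at pq = 0.10, h = 0.6.

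**What to change.** 1. Add one non-identifying field to 4.3.2 and 4.4.2: setting of test request (ED, inpatient, community or other).
2. For hospital and ED outcomes, state that the association analysis will be repeated with exposure from community-requested tests only.
3. Describe same-period associations that use all tests as descriptive, not as evidence that viruses predict presentations, and adjust the synopsis wording to match.
4. Lagged exposure may be added in the SAP, but should not be relied on alone to remove the overlap.

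**Cost.** One extra field per test from each laboratory, and lower precision in the community-only analysis. Adding the field before extraction is cheaper than returning to each laboratory for the 7 to 10 years of retrospective data sought under 11.1.

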# GLOSSARY OF ABBREVIATIONS

| PCR | Polymerase Chain Reaction |
| --- | --- |
| RSV | Respiratory Syncytial Virus |
| PIV | Parainfluenza Virus |
| hMPV | Human Metapneumovirus |
| Flu | Influenza |
| ED | Emergency Department |
| VAED | Victorian Admitted Episodes Dataset |
| VEMD | Victorian Emergency Minimum Dataset |
| PREDICT | Paediatric Research in Emergency Departments International Collaborative |
| RHEMMS | Rapid Health Emergency Medicine Monitoring System |
| POLAR | Population Level Analysis and Reporting Tool |
| VIDRL | Victorian Infectious Diseases Reporting Laboratory |

# Expected duration of study

The SNOTWATCH project will be an ongoing epidemiological analysis with no end date. Viability of the project will be assessed every four years.

Since the study initiation in 2019 and on-going enrolment of data partners, retrospective data will be sought from each participating Site/Data Partner dating back 7-10 years from the date of their enrolment into the SNOTWATCH project. Enrolment of sites for prospective data-linkage will remain open until the SNOTWATCH aims are met. The duration of this study for each participating site will be ongoing or as determined as per the research agreements. The PI will ensure that all HRECs and RGOs as well as regulatory and funding bodies have been notified at the closure of the SNOTWATCH project.

*See – Section 5. for Participant Withdrawal.*

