### 4.3.2. Microbiology results secure uploading

De-identifiable aggregated fields for each pathology tests will be uploaded into a secure REDCap

database with multi-factor authentication. The uploaded fields will be:

- Age in years (or less than one year of age: <6m, 6m-11m)
- Postcode of residence
- Gender
- Date of test
- All positive results for that test (e.g., RSV and influenza positive)

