### 11.3.1. Handling of missing data

If data is missing from a particular time frame or postcode, that block of time/ postcode will be removed from analysis.

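### Look-back counted from each partner's own enrolment staggers laboratory entry, and the listed microbiology fields carry neither a laboratory code nor test counts to separate entry from real change

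*Protocol*

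**What the plan says.** The section on expected duration asks each partner for past data "dating back 7-10 years from the date of their enrolment into the SNOTWATCH project". Section 11.1 repeats the rule as "attaining retrospective data within a timeframe of 7-10 years dating from the enrolment of each participating site/dataset". Entry is staggered and open-ended: the duration section refers to "Since the study initiation in 2019 and on-going enrolment of data partners" and adds that "Enrolment of sites for prospective data-linkage will remain open until the SNOTWATCH aims are met". No common calendar start is set for the microbiology data.

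The primary objective is a description over time and place of PCR positives from all participating laboratories, and section 2.1 speaks of amalgamating the results. Section 9.2.1 wants a historical baseline for later comparison. Sections 4.5.6 and 11.3 say that the share of the population covered is unknown.

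Section 4.3.2 introduces its list with "The uploaded fields will be" and names five items: age, postcode, gender, test date and positive results. Section 4.4.2 gives the same five for the prospective phase. Appendix 16.1 has tables for the clinical datasets but none for the pathology laboratories, so it adds no microbiology field.

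On gaps, section 11.3.1 says: "If data is missing from a particular time frame or postcode, that block of time/ postcode will be removed from analysis".

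**The concern.** A series pooled over contributors has a stable meaning only if the set of contributors is stable or can be adjusted for. Here the start of each laboratory's series is its enrolment date minus a length that itself varies, so the early years are likely to rest on fewer laboratories than the later ones. Positives would then rise while true activity stayed flat. With coverage unknown, there is no population denominator to absorb the change.

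At stake are the long-term trend in the primary description and the historical baseline. The field list cannot simply be left to the statistical analysis plan, because a later model cannot use a laboratory code or a test count that was never uploaded.

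**Working it through.** The protocol gives no calculation in 11.1, so there is no figure to reproduce. The check is calendar arithmetic.

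**Inputs from the protocol:** initiation in 2019; look-back of 7 to 10 years from each partner's enrolment; enrolment open; five upload fields.

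**Assumptions, not in the protocol:** equal-sized laboratories, constant true activity, whole calendar years, and the numbers of laboratories and last enrolment years shown below.

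**1. Spread of start dates.** Start = enrolment year − look-back.
- Same-day enrolment: 10 − 7 = 3 years apart at most.
- Earliest start: 2019 − 10 = 2009.
- Last enrolment 2021: latest start 2021 − 7 = 2014, spread 5 years.
- Last enrolment 2023: latest start 2016, spread 7 years.
- Last enrolment 2025: latest start 2018, spread 9 years.

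**2. Worked cases, six laboratories.**
- All with 10 years, two enrolling in each of 2019, 2020 and 2021: the number contributing in 2009, 2010 and 2011 is 2, 4, 6. Ratio 6/2 = 3-fold.
- All with 10 years, one enrolling each year from 2019 to 2024: 1, 2, 3, 4, 5, 6 over 2009 to 2014. Ratio 6/1 = 6-fold.
- Look-backs that lengthen with later enrolment (2019 with 7, 2020 with 8, 2021 with 9, 2022 with 10): all start in 2012. Ratio 1.0, no artefact.

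**3. Simulation.** There were 20 laboratories and 4,000 draws, with enrolment years equally likely from 2019 to the last year and look-backs of 7, 8, 9 or 10 years equally likely. The log of the number contributing was regressed on year from the first start to 2018. Artefactual trend = exp(slope) − 1.

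| Enrolment | Median trend per year | 95% of draws |
|---|---|---|
| all in 2019 | +12% | 7% to 22% |
| 2019–2021 | +23% | 13% to 34% |
| 2019–2024 | +33% | 20% to 45% |

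**4. Can the listed fields correct it?** Restricting to a constant set of laboratories, or fitting a laboratory intercept, needs a laboratory code. Percent positive needs negative results or a test count. Neither is listed. Postcode is a weak proxy, since several laboratories may serve one postcode.

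**5. Does 11.3.1 solve it?** There are two readings, and they exclude each other.
- A laboratory not yet contributing counts as missing data. Periods before the latest start are then removed. The set of laboratories is constant, but each new entrant shortens the baseline.
- It does not count as missing. A postcode served by another laboratory looks complete, nothing is removed, and the artefact stays.

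**6. After the change.** With one common start, no earlier than the latest start among the laboratories analysed, the number contributing is constant at the early end and the artefactual trend is 0% a year. If the last enrolment is in 2021, that start is 2014 at the latest. Fixing the look-back length alone is not enough: the 2, 4, 6 case already uses 10 years for all.

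**The case against.** Several counter-arguments have force.

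- **Source may be traceable.** Section 5.1 lets a withdrawing partner ask that its data not be used, which presupposes attribution, and section 9.2.1 describes a REDCap audit trail. A reader might infer that source and contribution dates are lost for good; the protocol does not show that. What stands is that it does not make source an analysis field, and the prospective uploads go to a different server.
- **Negative results may be available.** Section 9.2.1 mentions positive or negative results. If they are uploaded, percent positive removes much of the rise in raw counts, though not shifts in the mix of laboratories. The field lists show positives only, so the two places disagree.
- **Associations with health outcomes.** A reader might infer that these are biased too. But section 9.2.1 says that outcome entries are supplied from 24 July 2019. A laboratory with at least 7 years of look-back that enrols by 24 July 2026 (2019 + 7) already contributes on that date, so if the date stands the associations are largely shielded. An artefactual trend in virus counts also needs a trending outcome and a model without trend adjustment to create an association. The date does not fit a 7 to 10 year look-back and has to be reconciled.
- **The missing-data rule.** A reader might infer that following 11.3.1 literally produces the bias. It would instead leave a constant set of laboratories with a shorter baseline.
- **Analysis choices belong in the analysis plan.** This is true of intercepts and sensitivity sets, and section 11.2 announces such a plan. It does not cover fields that are not collected.
- **Seasonal shape** within a year is little affected by laboratories entering across years. This limits the point to longer trends and baseline levels.

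**Conclusion.** The point stands in this form: staggered laboratory entry follows from the look-back rule and open enrolment, and the listed fields cannot separate it from real change in pooled positives. Neither reading of 11.3.1 gives both a full baseline and a constant set of laboratories.

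The size is not determinable from the protocol. The 12% to 33% a year are medians under assumed equal laboratories, constant activity and evenly spread enrolment and look-backs. Larger figures can be built from other entry patterns, and alignment of the look-backs could bring the artefact to zero, although nothing in the protocol requires that alignment. The rise sits at the early end of the series. Partners that withdraw or supply no prospective data would cause a fall at the late end. No conclusion about virus-outcome associations can be drawn until the 24 July 2019 date is reconciled with the look-back rule.

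**What to change.** - In 4.3.2 and 4.4.2, add a coded laboratory identifier to the uploaded fields.
- Reconcile the mention of negative results in 9.2.1 with those lists, so that negative results or total tests are uploaded and percent positive can be used. This is also needed because section 2.1 says that wider and more sensitive testing has greatly increased positives; that drift occurs within laboratories, and neither a common start nor a laboratory intercept removes it.
- Keep a table of each laboratory's contribution start and stop dates.
- In the duration section and 11.1, state that the main time trends use a common calendar window with laboratories contributing throughout, or a within-laboratory analysis with laboratory intercepts. Use all laboratories as a sensitivity analysis.
- State in 11.3.1 whether a laboratory that is not yet contributing counts as missing.
- Reconcile the 24 July 2019 date in 9.2.1 with the look-back in the duration section and 11.1.

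The cost is protocol wording, one extra coded field that describes no patient, test counts if they are not already supplied, and the loss of some early records from the main trend analysis. Records uploaded before the code is added may have to be traced back to their source.
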